## Abstract

**Background:**

Necrotizing enterocolitis (NEC) is the leading cause of death among preterm infants born at < 30 weeks’ gestation. The incidence of NEC is reduced when infants are fed human milk. However, in many neonatal intensive care units (NICUs), it is standard practice to freeze and/or pasteurize human milk, which deactivates bioactive components that may offer additional protective benefits. Indeed, our pilot study showed that one feed of fresh mother’s own milk per day was safe, feasible, and can reduce morbidity in preterm infants. To further evaluate the benefits of fresh human milk in the NICU, a randomized controlled trial is needed.

**Methods:**

Our prospective multicenter, double-blinded, randomized, controlled trial will include infants born at < 30 weeks’ gestation and admitted to one of 29 tertiary NICUs in China. Infants in the intervention (fresh human milk) group (*n* = 1549) will receive at least two feeds of fresh human milk (i.e., within 4 h of expression) per day from the time of enrollment until 32 weeks’ corrected age or discharge to home. Infants in the control group (n = 1549) will receive previously frozen human milk following the current standard protocols. Following informed consent, enrolled infants will be randomly allocated to the control or fresh human milk groups. The primary outcome is the composite outcome mortality or NEC ≥ stage 2 at 32 weeks’ corrected age, and the secondary outcomes are mortality, NEC ≥ stage 2, NEC needing surgery, late-onset sepsis, retinopathy of prematurity (ROP), bronchopulmonary dysplasia (BPD), weight gain, change in weight, increase in length, increase in head circumference, time to full enteral feeds, and finally, the number and type of critical incident reports, including feeding errors.

**Discussion:**

Our double-blinded, randomized, controlled trial aims to examine whether fresh human milk can improve infant outcomes. The results of this study will impact both Chinese and international medical practice and feeding policy for preterm infants. In addition, data from our study will inform changes in health policy in NICUs across China, such that mothers are encouraged to enter the NICU and express fresh milk for their infants.

**Trial registration:**

Chinese Clinical Trial Registry; #ChiCTR1900020577; registered January 1, 2019; http://www.chictr.org.cn/showprojen.aspx?proj=34276

## Background

Necrotizing enterocolitis (NEC) is a severe inflammatory disorder of the intestine that primarily affects very low birth weight (< 1500 g) or very preterm infants (≤ 32 weeks’ gestation); it is also the leading cause of death in the neonatal intensive care unit (NICU) [1, 2]. Between May 1, 2015, and April 28, 2018, we found that the incidence of mortality in infants born at < 30 weeks’ gestation at 25 hospitals in China was 25%, and the incidence of NEC was 6.2% [[name], written communication, October 2018]. Elsewhere, the overall mortality from NEC was reported to range from 15 to 30%, with more severe cases of NEC resulting in a higher mortality rate. For infants who survive, a significant risk exists for long-term complications and morbidity, including impaired neurodevelopment [1, 2].

Currently, no known effective treatment exists for NEC. Infants are initially managed medically through bowel rest (cessation of oral feeds), abdominal decompression, administration of broad-spectrum antibiotics, and provision of supportive care including parenteral nutrition, ventilator support, and blood transfusions as necessary. Should bowel perforation occur, then surgery is required to remove damaged tissue and gas build up through laparotomy, primary peritoneal drainage, or both [1, 2].

The World Health Organization and others have advocated for the use of mother’s own milk to prevent NEC [3–5]. Human milk contains both nutritional components (e.g., proteins, amino acids, fats, carbohydrates, vitamins, and minerals) and bioactive components (e.g., live immune cells, cytokines, hormones, and growth factors) that have antimicrobial and anti-inflammatory properties [6, 7]. More recently, Hassiotou (now Kakulas) et al. [8] showed that human milk is a rich source of pluripotent stem cells that, when ingested by the infant, enter the blood stream and are incorporated into the major organ systems of the infant. Although their exact function still remains unknown, breast milk stem cells possibly benefit the infant through actively participating in growth and/or regeneration. The current evidence strongly suggests that fresh human milk may have a significant protective effect against both infection and NEC [9].

When the mother’s own milk is not available, the next best option is donor human milk, and the last option, formula. The use of formula in low birth weight or very preterm infants was reported to increase the risk of developing NEC when compared with donor human milk [10]. Although human milk, either mother’s own or donor milk, appears to be the best feeding source for the nutrition, immunoprotection, and development of the preterm infant, current practices related to the handling and use of human milk in the NICU raise questions about whether we are deriving the maximum benefit from its use. Currently, in many NICUs worldwide, milk expressed by mothers of preterm infants is frozen and stored prior to use. When the infant requires oral feeds, frozen milk is defrosted and warmed, fortifier is added as needed, and the milk is then fed to the infant. Freezing human milk at either − 20 °C or − 80 °C and for longer times decreases the energy content and amount and bioactivity of several important components of human milk [11, 12], including the fat, carbohydrates, secretory immunoglobulin A, lactoperoxidase, lysozyme, antibacterial factors, and antioxidants [11–18]. In addition, defrosted human milk does not contain any live stem cells because they have a half-life of approximately 4 h and die when human milk is frozen and/or heated [8].

The current NICU human milk feeding procedure exists as a means of ensuring that infants have consistent access to their mother’s milk even if the mother is not able to spend time in the NICU. The process also allows for stricter quality and infection control, computerized inventory, and monitoring via electronic health records. However, this same process deprives infants of the benefits of the cellular content of human milk, including immune cells, stem cells, and the protective effects of the plethora of bioactive immunological components [8].

We recently conducted a pilot study entitled “Testing the feasibility and safety of feeding preterm infants fresh mother’s own milk in the NICU: a pilot study,” where we evaluated the feasibility and safety of providing preterm infants (born at < 30 weeks’ gestation) with at least one daily feed of fresh mother’s own milk, within 4 h of expression, until they reached 32 weeks’ corrected age [19]. The results showed that one feed of fresh human milk per day was both safe and feasible in the NICU, and it reduced morbidity among infants of < 30 weeks’ gestation.

## Methods/Design

### Study design

Our study will be a prospective, multicenter, blinded, randomized, controlled trial (RCT) designed in accordance with the Standard Protocol Items: Recommendations for Interventional Trials (SPIRIT 2013; Additional file 1) [14] and the Consolidated Standards for Reporting of Trials CONSORT guidelines [16]. Mothers who consent to participate in the study will be randomly assigned to the intervention (fresh milk) group or the control group. In the fresh milk group, mothers will be asked to provide at least two feeds of fresh milk (i.e., within 4 h of milk expression) per day. In the control group, mothers will follow the usual protocol for the collection, freezing, and use of human milk, and the current NICU standards of human milk handling and feeding will apply.

### Study population

The study population will include infants born at < 30 weeks’ gestation who never received infant formula, are admitted to one of the 29 participating tertiary NICUs in China, have parents who consent to the study, and have mothers who are willing to provide at least two feeds of fresh milk daily, 7 days a week until the infant is 32 weeks’ corrected age. Infants with major congenital anomalies or receiving palliative care, infants with mothers who are too ill to provide fresh human milk in the first week postpartum or are unable to provide at least two feeds of fresh milk a day, infants with congenital *Cytomegalic virus* (CMV) infection, and infants whose mothers have blood CMV-IgM (+) or CMV-DNA (+) or are unwilling to consent will be excluded. Congenital CMV-infection is defined as positive CMV NAT (or positive viral culture obtained from clinician-ordered testing) in blood or urine within 2 weeks of life [20].

China is a large country with four municipalities, 23 provinces, and five autonomous regions, and we were able to recruit 29 tertiary NICUs of the same academic level from 18 provinces, municipalities, or autonomous regions to participate in our study. All hospitals have milk banks, are located in cities of a similar size with above-average economic status and similar patient mix, and admit on average an estimated 2397 infants per year who would be eligible for the study [[name], written communication, October 2018]. The following hospitals have committed to participate in the RCT: Children’s Hospital Affiliated to Zhengzhou University, Children’s Hospital of Fudan University, the Affiliated Obstetrics and Gynecology Hospital of Nanjing Medical University and Nanjing Maternity and Child Health Care Hospital, Children’s Hospital of Nanjing Medical University, Guizhou Maternity and Child Health Care Hospital, Shanghai First Maternity and Infant Hospital, The Women and Children’s Health-Care Hospital of Hubei Province, Henan Provincial People’s Hospital, Northwest Women and Children Hospital, The First Affiliated Hospital of Zhengzhou University, Shenzhen Maternity and Child Healthcare Hospital, Maternal and Child Health Hospital of Guangxi Zhuang Autonomous Region, Xinjiang Uiger Municipal People’s Hospital, Children’s Hospital of Soochow University, Women’s Hospital School of Medicine Zhejiang University, Qilu Children’s Hospital of Shandong University, Xiamen Children’s Hospital, Children’s Hospital School of Medicine Zhejiang University, The Third Affiliated Hospital of Zhengzhou University, Woman and Children Hospital of Zhengzhou, Anhui Provincial Hospital, Xianmen Humanity Hospital, Children’s Hospital of Capital Institute of Pediatrics, Guangdong Women and Children Hospital, Jiangxi Children’s Hospital, First Affiliated Hospital of Xinjiang Medical University, Shanghai General Hospital and Shanghai Jiaotong University, Gangdong Maternal and Child Health Care Hospital, Guangzhou Women and Children’s Medical Center, and Children’s Hospital of Hainan Province.

### Enrollment

Clinicians will approach eligible mothers for consent at their first visit to the NICU following their infant’s admission. The clinicians will explain the study verbally and deliver printed information sheets describing the purpose and process of the study (Fig. 1). Enrollment will occur before the infant’s first oral feed and after the parents give consent (Additional file 2). Infants whose parents decline to consent will receive standard care.

**Fig. 1 Fig1:**
[figure not shown]
SPIRIT 2013 Schedule of infant enrollment, intervention, and assessment. Abbreviations: *-T1* enrollment phase, *T1* baseline assessment, *T2* 32 weeks’ corrected age, *T3* completion phase, *NEC* necrotizing enterocolitis, *ROP* retinopathy of prematurity, *BPD* bronchopulmonary dysplasia

### Feeding intervention

#### Standard feeding and fortification procedures

Infants born at < 30 weeks’ gestation are initially provided with nutrition intravenously (total parenteral nutrition [TPN]). If the infant is not suffering from any condition that affects the function of the gastrointestinal system, oral feeds are introduced as early as possible. Human milk is introduced into the stomach through a nasogastric tube according to a schedule that is dependent on the infant’s weight at birth. The amount of milk is very small at first, then it is gradually increased if the infant tolerates the milk well. The frequency of feeding varies, but it is most often every 2 or 3 h, depending on the weight of the infant. As the volume of milk increases, the volume of TPN is decreased until the infant receives all their nutrition from human milk.

Once the infant’s total nutrition is from human milk (“full enteral feeds” is defined as 120 ml/kg/day), fortifiers and other nutritional supplements are added to each feed. The first supplement added is human milk fortifier; 4 days later, extra protein is also added; and then after another 3 days, vitamins and iron are added to each feed (Additional file 2).

Mother’s own milk is the food of choice, followed by human donor milk. The decision to supplement the mother’s own milk with donor milk is dependent on the mother’s ability to produce milk in sufficient quantity for all feeds. Often in the first few days of life preterm infants are fed donor milk as the mother may not start producing milk right away or may still be recovering from the birth. Mothers may also produce less milk than is needed, either initially or throughout the breastfeeding period, so some feeds may be supplemented with donor milk.

Current standard procedure dictates that in every case where expressed human milk is used, the milk is collected from the mother and frozen in the milk preparation room. Each evening the feeds for the following day are ordered, and milk is defrosted and prepared. Infants move from enteral feeds to breastfeeding when they are clinically judged to be able to do so.

#### Fresh milk feeding and fortification procedure

The exact same standard feeding and fortification procedures (timing of initiation, amount, frequency, and supplementation with human donor milk as needed) will be followed for infants in the fresh milk group, with the one exception that at least two feeds per day will be fresh milk until the infants are 32 weeks’ corrected age. “Fresh” milk is defined as human milk that has not been frozen, chilled, or pasteurized and has been expressed less than 4 h prior to feeding the infant. The 4-h time window allows us to retain live human milk cells that have a 4-h half-life.

#### Human milk collection

In both the control and fresh milk groups, all mothers will be present in the NICU to pump milk for a “fresh” feed at least two times per day, 7 days a week, using the Medela Symphony breast pump. Human milk will be expressed into a sterile plastic container as per standard NICU protocol. The container will be labeled with the mother’s bar code and immediately given to a research nurse dedicated to the implementation of this study. The research nurse will take the milk to the milk preparation area where the details of the milk and feeds will be entered into a database, and then she will prepare the milk and deliver it to the NICU, where the infant’s nurse will feed the infant. Milk being prepared for a fresh feed will not be heated but will be kept at room temperature at all times.

Any additional milk expressed by the mother in the NICU or at home that exceeds the 4-h fresh-milk window will be transferred to a sterile container, frozen, and stored in the milk preparation room for use when the mother is not available to provide fresh milk. Human milk collection and handling of previously frozen milk will follow standard NICU protocol. Mothers who provide fewer than 2 feeds of fresh milk every day will remain in the study per intention-to-treat principles. Furthermore, retaining mothers who do not produce enough milk will enable us to calculate the percentage of mothers who can produce at least two feeds of fresh milk a day, which in turn, allows us to determine the feasibility of standard fresh milk guidelines.

Mothers in both the control and fresh milk groups will continue to provide human milk in the manner described from the time the infant is able to tolerate enteral feeds until the infant is 32 weeks’ corrected age. Mothers will also be encouraged to express human milk when they are away and bring it into the NICU, as per standard NICU protocols. In cases where a mother is not able to produce enough human milk for all her infant’s feeds, the remaining feeds that are not being provided as fresh or frozen mother’s own human milk may be supplemented using human donor milk.

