### Sample size

The sample size justification was based on the primary outcome and the hypothesis. A recent quality improvement study found that the incidence of the composite outcome mortality or NEC ≥ stage 2 was 29% in 25 Chinese NICUs [[name], written communication, October 2018]. Assuming a primary outcome rate of 29% for the control group, we estimated that a sample size of 3098 (1549 patients per arm) will achieve an 80% power to detect at least a 16% relative reduction in the incidence of the primary outcome in the fresh milk group when compared to the control group. With an average of 2397 eligible infants admitted to participating hospitals each year and an estimated enrollment rate of 60%, we expect to recruit 1438 infants per year and the study to take 2 years. We used the chi-square test for the power analysis, assuming a significant level of 0.05. Therefore, the proposed enrollment of 3098 patients will have sufficient power to test our hypothesis taking into account a possible 5% data loss to follow-up.

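### The percentage of mothers able to give two fresh feeds a day is taken among mothers already screened for it, so it overstates how feasible a general fresh-milk guideline would be

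*Protocol article*

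**What the plan says.** Two parts of the protocol article use the same condition, two fresh feeds a day, for different purposes.

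- **Entry.** In Study population, infants qualify if they "have mothers who are willing to provide at least two feeds of fresh milk daily, 7 days a week", up to 32 weeks' corrected age. The exclusions include "infants with mothers who are too ill to provide fresh human milk in the first week postpartum or are unable to provide at least two" (the count refers to fresh feeds per day).
- **Estimation.** In Human milk collection, enrolled mothers who fall below two fresh feeds stay in the study under intention to treat. The article adds that keeping them will "enable us to calculate the percentage of mothers who can produce at least two feeds of fresh milk a day", and that the resulting figure "allows us to determine the feasibility of standard fresh milk guidelines".

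The Enrollment section places consent and enrolment before the infant's first oral feed. Nothing in the article limits the percentage to willing and able mothers, and nothing brings screened-out mothers back into the denominator.

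**The concern.** The quantity to be estimated is also a condition of entry. Retaining low producers recovers only mothers who passed the screen and later fell short. Mothers who failed at the screen are absent from both numerator and denominator.

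This group may not be negligible. The Standard feeding and fortification procedures section acknowledges that mothers of these infants may be slow to start producing milk or may still be recovering from the birth. Mothers in that position in the first week are among those whom the entry criteria can remove.

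What is at stake is one interpretive claim. Followed as written, the trial would report how often mothers chosen as willing and able manage two fresh feeds a day, and would present that as the feasibility of a standard guideline.

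**Working it through.** The article states no value for this percentage, so there is no figure to reproduce. The check compares the two sections and then works out the direction and size of the error.

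**Notation.** Take all otherwise eligible mothers, meaning those whose infants meet every criterion unrelated to milk provision.
- e = share screened out as too ill or unable. Not given in the article.
- d = share who are unwilling or decline consent. Not given in this form.
- F = percentage of enrolled mothers who manage two fresh feeds a day. Not given; it is what the trial would report.

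**Step 1: direction.** Suppose screened-out mothers count as not able, and mothers who are unwilling or decline would have done as well as those enrolled. Then

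feasibility among otherwise eligible mothers = F × (1 − e).

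This is below F for any e > 0. If some screened-out mothers could have managed later, the result still lies below F as long as they would have succeeded less often than enrolled mothers.

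**Step 2: relative size.** Overstatement = F / [F × (1 − e)] = 1/(1 − e), whatever F is. Both e and F below are assumed.

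| Assumed e | 1/(1 − e) | F = 90% becomes | F = 80% becomes |
|---|---|---|---|
| 5% | 1/0.95 = 1.05 | 0.90 × 0.95 = 85.5% | 0.80 × 0.95 = 76% |
| 10% | 1/0.90 = 1.11 | 0.90 × 0.90 = 81% | 0.80 × 0.90 = 72% |
| 20% | 1/0.80 = 1.25 | 0.90 × 0.80 = 72% | 0.80 × 0.80 = 64% |
| 30% | 1/0.70 = 1.43 | 0.90 × 0.70 = 63% | 0.80 × 0.70 = 56% |

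**Step 3: the unwilling and decliners.** Refusing a randomized trial, or a commitment seven days a week, is not the same as being unable to produce milk. The rate in this group is unknown, so it can only be bounded:
- lower bound (none could): F × (1 − e − d)
- upper bound (all could): F × (1 − e − d) + d

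The upper bound exceeds F when d × (1 − F) > e × F. Non-enrolment by choice therefore does not by itself show overstatement. The certain part of the argument rests on e alone.

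**Step 4: reach.** The percentage enters neither the sample size calculation (1549 per arm) nor the chi-square comparison of the primary outcome, so neither changes.

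**The case against.** **It is not a trial aim.** This stands. The objective in the Background and the list in Outcomes measures do not include the percentage, and Statistical analysis gives it no method. It appears as a second reason for keeping low producers. The article nevertheless commits to the calculation and to a conclusion from it.

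**The screen is early and imperfect.** This also stands. Ability is judged before the first oral feed, and the article expects some enrolled mothers to fall short. The figure is therefore not bound to be near 100%, and it is informative about enrolled mothers. It still leaves out failures at screening.

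**An article can leave the denominator to the full protocol, and CONSORT flow reporting will show exclusions.** Partly right. Study design commits to CONSORT, so screening counts may be at hand. But the text ties the calculation to retained mothers and draws the guideline conclusion from it, and nothing in the article links it to screening counts.

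**Stronger readings that the article does not support:**
- A reader might combine the 60% enrolment rate (Sample size) with the 10% drop-out (Discussion) to get 0.60 × 0.90 = 54% up to 54% + 40% = 94%, against a reported 90%. This treats staying in the study as meeting the schedule, yet low producers stay by design. The 10% comes from a pilot that asked for one fresh feed a day. The range also contains 90%, so it shows no overstatement. The article does not say why 40% would not enrol, or whether the eligible count already reflects the maternal criteria.
- A reader might lower that range for mothers already excluded, to 0.54 × 0.90 = 49% or 0.54 × 0.70 = 38%. The 10% to 30% exclusion is an assumption, and applying it only to the lower end shows only the worst case. The upper end would become 0.94 × 0.90 = 85% or 0.94 × 0.70 = 66%.
- A reader might infer that this percentage will drive the policy change foreseen in the Abstract. That passage speaks of the study's data in general, after an aim concerned with infant outcomes, and does not mention the percentage.

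**Conclusion.** The concern holds as a fault in one ancillary figure. A percentage taken among enrolled mothers cannot determine the feasibility of a guideline for mothers in general, because inability to give two fresh feeds a day is itself a ground for exclusion. The bias is upward, provided that mothers screened out as too ill or unable would succeed less often than those enrolled.

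Its size cannot be computed from the article. With those mothers counted as not able, it is a factor 1/(1 − e), or 1.05 to 1.43 for assumed e of 5% to 30%. The effect of those who are unwilling or decline can only be bounded, and its direction is not known. The randomized comparison, the significance level, the power and the sample size are unaffected.

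**What to change.** 1. In Human milk collection, describe the in-trial percentage as applying to enrolled mothers, who were willing and judged able at entry. Do not present it alone as the feasibility of a guideline.
2. For any statement on guideline feasibility, take all otherwise eligible mothers as denominator. Leave out families excluded for major anomalies, palliative care or CMV, since those exclusions have nothing to do with milk production. A denominator of every screened mother of an infant under 30 weeks would be too wide.
3. Count mothers screened out as too ill or unable as not able. Show those unwilling or declining consent as the lower and upper bounds of Step 3.
4. Record the reason for non-enrolment (too ill, unable, unwilling, consent declined) on the screening log during recruitment, because it may be hard to recover later.

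The cost is one more reason field on the log, a change of wording, and a less favourable feasibility figure. Eligibility, feeding procedures, sample size and the primary analysis stay as they are.
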